### Survey tool and variables

2.7

The survey is structured in five main sections (sociodemographic, health-related quality of life, critical health literacy, social connectedness, community capital, and knowledge, attitudes and practices on personal antibiotic use). The first section, which collects sociodemographic characteristics, will always be administered at the beginning of the survey. Participants will self-fill these questions on the interviewer's device, unless they request assistance, in which case the interviewer will read them out. This sociodemographic information will be used to analyse health inequalities within the study area, disaggregating the results by relevant social groups (by age, country of birth, race/ethnicity, sex, gender, etc.) and calculating both absolute and relative inequalities. The remaining four sections will be presented in a random order for each participant, using an algorithm embedded in the electronic form. This randomization of the remaining four sections (health-related quality of life, critical health literacy, social connectedness, community capital, and knowledge, attitudes and practices regarding personal antibiotic use) will allow the random and equitable distribution of potential biases in the understanding and answering of the questions, especially those at the end of the survey. The complete survey tool, variables, and response options can be found at the Supplementary Information of this protocol (Supplementary Supplementary Tables S2–S7).

The main outcome of the surveys is the health-related quality of life (HRQoL) measured using the VR-12 questionnaire. This tool has been internationally validated to measure HRQoL e (14). The VR-12 questionnaire contains 12 items that assess 8 aspects of health-related quality of life: physical functioning, physical role, bodily pain, general health, vitality, emotional role, social functioning and mental health. The VR-12 questionnaire measures these aspects in scales to produce a summary score in two dimensions: a physical dimension, represented by the Physical Component Summary, and a mental dimension, represented by the Mental Component Summary.

In addition, as secondary variables, a series of indicators will be measured with a descriptive and analytical purposes to also guide the co-creation process and a complementary role in the impact assessment as intermediate outcomes.

*Critical Health Literacy (CHL)*. We will measure CHL (15) using the All Aspects of Health Literacy Scale (AAHLS) (16) after analyzing the psychometric properties of a new version adapted to Spain. CHL comprehends the capacity to critically analyze health determinants, reflect on socioeconomic and cultural contexts, which promotes advanced personal skills, interactive engagement with health systems, informed decision-making, empowerment, and the effectiveness of health promotion interventions (17, 18).

*Community capital*. We have developed a tool to measure the perception and use of community resources, defined as “any factor (or resource) that enhances the capacity of individuals, groups, communities, populations, social systems and institutions to maintain and sustain health and wellbeing and helps them to reduce health inequalities” (8). The tool classifies resources in seven categories: 1. Natural, 2. Cultural, 3. Human, 4. Social, 5. Built, 6. Financial and 7. Political, in line with the community assets literature (19, 20). Participants will be asked to describe the resources in their environment (neighborhood where they live, and other places in the municipality that they frequent) in each category, and the interviewer will record yes or no accordingly (Supplementary Table S5). We will then ask participants about the frequency of use and when appropriate, the perceived barriers that prevent them from making more use of these community assets. The list of potential barriers was prepared based on literature review (21, 22). The instrument was pre-tested to obtain feedback on the clarity and relevance of the questions in order to make any necessary adjustments before its final implementation.

*Social capital and community cohesion*. Here, we draw on items from a previously validated scale on bridging social capital used in the United States with Latino immigrant populations (23), complemented by selected questions adapted from the Canadian Community Health Survey (24), related to a sense of belonging to one's community and trust. The resulting instrument was tested through a pilot study, and its psychometric properties will be evaluated to ensure its validity and suitability for our local context.

*Knowledge, attitudes and practices (KAP) on personal antibiotic use*. We will measure KAP on personal antibiotic use using an instrument validated in Spain (25). This will enable us to obtain an analysis of common antibiotic-related behaviors by analyzing the following three dimensions: knowledge (what respondents know about antibiotics), attitude (what respondents think about antibiotics) and practice (what they do regarding antibiotics).

For the new validated versions of AAHLS, social capital and community cohesion, and community capital scales, a pilot test will be conducted on 20 participants to evaluate the clarity of the adapted version of the questionnaire before conducting the survey. The initial versions were subsequently reviewed by an external panel of experts in epidemiology, psychology and both English and Spanish languages to refine the translation and minimize potential misunderstandings among respondents.

To analyse their psychometric properties, we will use Cronbach's alpha, Confirmatory Factor Analysis (CFA) and bivariate analyses. Cronbach's alpha will assess the internal consistency of each scale. CFAs will be conducted to evaluate whether the data fitted the theoretical factor structure proposed by the original scales of AAHLS and social capital and community cohesion as well as the proposed structure of the community capital tool. Model fit will be evaluated using standard indices. The Comparative Fit Index (CFI) and Tucker–Lewis Index (TLI) will assess the relative improvement of the tested model over a null model, with values approaching 0.90 indicating acceptable fit. The Root Mean Square Error of Approximation (RMSEA) will evaluate absolute model fit, with lower values indicating better approximation of the data. Finally, bivariate analyses will complement the CFA by examining expected associations between scale scores and sociodemographic variables.

### Data analysis

2.8

As main outcome, the mean and the standard deviation of the health-related quality of life will be calculated and stratified by sex, age group and other sociodemographic variables, thus allowing for an equity analysis. In addition, we will perform multivariate models to analyse the association of sociodemographic characteristics on health-related quality of life and secondary variables (critical health literacy, social capital, community capital, and knowledge, attitudes and practices on personal antibiotic use). These results will be also crucial to enrich the discussions in the co-creation process, facilitating an equitable and contextualized approach to the identified health issues. A before-and-after analysis will also be carried out using the population-based survey data to assess changes across time points (pre- and post-intervention) in the population in both main and secondary variables, providing evidence on the evolution of health-related quality of life and other relevant social determinants of health. Specifically, firstly, the normal distribution of physical and mental HRQoL will be tested by conducting Shapiro-Wilk tests and plotting histograms. In case of observing a non-normal distribution, these variables will be dichotomised using the median value of the whole sample (pre- and post-intervention). Therefore, given the distribution of health-related quality of life, multivariate linear regression models or Poisson regression models with robust standard errors will be used to estimate absolute and relative changes across time points. Additional models will be run, including interaction terms of time with sex, age group and other sociodemographic variables to assess the changes in social inequalities in HRQoL. Contextual variables will be included, such as economic development, unemployment rate and poverty rate at the regional level of the province of Alicante before and after the intervention, retrieved from the National Institute of Statistics (INE) and the statistics portal of the Valencian Community in Spain. Statistical analysis will be adjusted for sex, age group and other sociodemographic variables such as education, ethnicity, migration status, household income, employment status and marital status, among others. Multiple imputation will be used for missing data on HRQoL and secondary variables. For the remaining covariates, an additional category of missing values will be created to include these individuals in the statistical analyses.

For statistical analysis, we will use the latest version of Stata/SE (StataCorp, Texas, USA), and R: A language and environment for statistical computing (R Foundation for Statistical Computing, Vienna, Austria). The *p*-value obtained in the hypothesis tests performed will be described. Although we will use a *p*-value < 0.05 as a reference to identify statistically significant differences, this value should be interpreted with caution when subgroup stratified analyses with smaller sample sizes are conducted. The possibility of a type II error (false acceptance of the null hypothesis) will be considered, allowing for a more nuanced and contextualized interpretation of the results, thus avoiding the premature exclusion of potentially relevant trends in under-represented subgroups. No survey weights will be used in statistical analyses.

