### Sample size estimation and selection criteria

2.4

The sample size has been calculated assuming that the prevalence of the variables of interest (e.g. proportion of individuals with poor health-related quality of life, proportion of individuals with limited critical health literacy etc.) does not exceed 30%, with an absolute precision of ± 5% and a confidence level of 95%. A design effect of 1.5 has been applied, following the recommendations of the World Health Organization's (WHO) STEPS guidelines (13) for complex designs. In addition, a rejection rate of up to 20% has been considered, implying the need to recruit at least 590 participants. The proposed inclusion of 600 participants also ensures the estimation of indicators for specific subgroups (such as by sex) with an absolute precision of close to ± 5%.

A before-and-after analysis will be conducted with 600 independent participants at each time point, selected using comparable samples and applying the same inclusion criteria and sampling design. This sample size is sufficient to detect significant differences in both our main outcome (i.e., health-related quality of life) and secondary variables. In the case of health-related quality of life, it allows us to identify absolute changes of around 10%, with a confidence level of 95% and a statistical power close to 80%. The exact power will depend on the initial prevalence of the indicator and the magnitude of the observed effect. Although the analysis of social inequalities may have lower power due to stratification by subgroups, we estimate that the sample size will be sufficient to identify relevant trends and significant differences in social inequalities in the studied sample.

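### A normality check with no stated threshold decides whether the main before-after comparison is a mean difference or a split at the pooled median; the split adds no validity and gives up power

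*Protocol article*

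**What the plan says.** The main outcome is health-related quality of life by the VR-12, summarised as a physical and a mental component score (section 2.7). Section 2.8 first treats it as continuous: "As main outcome, the mean and the standard deviation of the health-related quality of life will be calculated". For the before-after analysis it then applies a check to the scores themselves, using Shapiro-Wilk tests and histograms. It gives no threshold for calling a distribution non-normal, and does not say whether the check is run on the pooled data or on each survey. The consequence is fixed: "In case of observing a non-normal distribution, these variables will be dichotomised using the median value of the whole sample (pre- and post-intervention"). A linear model follows if the scores pass. Poisson regression with robust standard errors follows if they do not.

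Section 2.4 sets the size: "A before-and-after analysis will be conducted with 600 independent participants at each time point", and "A design effect of 1.5 has been applied". For the main outcome it says the sample can "identify absolute changes of around 10%, with a confidence level of 95% and a statistical power close to 80" per cent. It gives no mean, standard deviation or skewness for the VR-12 scores.

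**The concern.** The two branches answer different questions. One estimates a difference in mean score; the other estimates a change in the proportion above a cut that the sample itself sets. Which question is answered depends on how the data look, under a rule with no stated criterion.

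The check also looks at the wrong quantity. Linear regression makes no assumption about the marginal distribution of the scores, and with several hundred people per survey its inference on a mean does not lean on normal residuals either. The cut pools both surveys, so it cannot be known before 2029, it moves with the change it is meant to measure, and it marks no clinically defined state. At stake are a clear estimand for the main outcome and the power that a continuous score offers. The time-by-subgroup models for inequalities use the same outcome, and section 2.4 already expects lower power there.

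**Working it through.** **Inputs.** From section 2.4: 600 independent participants per survey, design effect 1.5, 95% confidence (taken as two-sided alpha 0.05), a change of about 10%, power close to 80%. Effective size per survey: 600/1.5 = 400. Assumed, because the documents are silent: 600 analysed per survey, a pure shift in location, no covariates, and reflected-gamma scores where skewness is needed.

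**1. The plan's own figure.** Two-proportion power = Φ[(Δ − 1.96·SE0)/SE1], where SE0 uses the pooled proportion and SE1 the separate ones. With 400 per survey:
- 50% to 40%: SE0 = √(2·0.45·0.55/400) = 0.03518, SE1 = √((0.25 + 0.24)/400) = 0.0350, so (0.10 − 0.06895)/0.0350 = 0.887 and power is 81.3%.
- 45% to 55%: SE0 = √(2·0.25/400) = 0.03536, SE1 = √(2·0.2475/400) = 0.03518, so power is 80.9%.

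The stated figure is reproduced, and it is already the power of an outcome split near 50%.

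**2. Does a mean comparison need the check?** In 20,000 simulated comparisons per setting, with 400 or 600 per survey and skewness 0, −0.5, −0.8 and −1.0, the t-test's type I error was 4.9% to 5.3%. The median split's was 5.5% to 5.7%. The fallback brings no gain in validity.

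**3. How easily does Shapiro-Wilk reject?** (1,000 runs each, 5% level)

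| Skewness | n = 600 | n = 1,200 |
|---|---|---|
| 0 | 6% | 5% |
| 0.1 | 13% | 23% |
| 0.2 | 42% | 72% |
| 0.3 | 76% | 97% |
| 0.5 | 99.8% | 100% |

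A separate run at n = 1,200 and skewness 0.1 gave 21%.

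**4. Power given up by the split, normal shape, 400 effective per survey.** Continuous score: power = Φ(d/√(2/400) − 1.96), with √(2/400) = 0.0707. Split: Δ = 2Φ(d/2) − 1, then the formula in step 1.
- d = 0.251 SD (moves the split from 45% to 55%): continuous Φ(3.554 − 1.96) = 94.5%, split 80.9%, loss 13.6 points.
- d = 0.198 SD: continuous Φ(2.80 − 1.96) = 80.0%; Δ = 0.0789, split 60.7%, loss 19.3 points.

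**5. Dependence on shape.** The efficiency of the split relative to the mean is 4·f(median)²·variance, which is 2/π = 0.637 under normality.

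| Skewness | Relative efficiency | Loss when continuous power is 80% | Loss when it is 95% |
|---|---|---|---|
| 0 | 0.637 | 19.2 | 13.0 |
| 0.5 | 0.652 | 18.1 | 12.1 |
| 0.8 | 0.679 | 16.4 | 10.6 |
| 1.0 | 0.704 | 14.8 | 9.3 |
| 2.0 | 1.000 | 0 | 0 |

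Simulated losses were slightly smaller: at 400 per survey and normal shape, 17.4 points at d = 0.198 and 12.1 at d = 0.25. The split's slightly raised type I error accounts for part of this.

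**6. Without the design effect** (600 per survey, 45% to 55%): continuous 99.2%, split 93.5%, loss 5.7 points.

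**The case against.** Several defences hold, and they limit the point.

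- **Promised power is kept.** A reader might infer that the fallback leaves the study underpowered. The documents do not support that: for a 10-point change the split has 80.9% power, as stated. The 19-point loss belongs to a shift of about 0.20 SD, and the plan states no effect size in SD units.
- **The switch is not certain.** A reader might infer that it will almost surely be triggered. That requires skewness of about 0.3 or more, or some other departure from normality, and the documents report no VR-12 distribution. Histograms are also used, so analysts could set aside a trivial rejection. The fair criticism is an undefined rule, not automatic switching on a p-value.
- **The 30% planning prevalence is not breached in any way that matters.** A reader might set the roughly 50% prevalence of a median split against "does not exceed 30%, with an absolute precision of" 5 points, which covers "proportion of individuals with poor health-related quality of life". That figure serves the single-survey precision calculation: 1.96²·0.3·0.7/0.05² = 322.7, times 1.5 = 484, then 605 (divided by 0.8) or 581 (times 1.2), which brackets the stated 590. At 50% prevalence the precision is 1.96·√(0.25/400) = 4.9 points, still within target, and the power statement separately says that it depends on the initial prevalence.
- **Means are still reported.** They are to be described whatever the check shows. That the two component scores would end on different scales is possible, but the wording can be read as treating them together.
- **The comparison is modest in aim.** The abstract calls it exploratory, and the discussion concedes that there is no control area.

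None of this gives a reason for the check. It reduces the point from a threat to validity to a loss of clarity and efficiency.

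**Conclusion.** The point holds as something that should be fixed, not as an error that undermines the study. An unquantified check makes the estimand of the main before-after comparison data-dependent, and its fallback gives no protection that a sample of this size needs. If the split is used, the power lost against the continuous score is about 12 to 19 points for near-normal to mildly skewed scores and about 9 to 15 at skewness 1. Both ranges take 400 effective per survey and continuous power of 80% to 95%. The loss is about 6 points for a 10-point change at 600 per survey without the design effect, and it vanishes near skewness 2. These figures rest on independent observations at the effective size, a location shift, no covariates and an assumed shape. The probability of the switch remains unknown.

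**What to change.** In section 2.8, delete the normality-triggered dichotomisation. State that the physical and mental component scores will be analysed as continuous by linear regression with robust standard errors whatever their distribution, and that the adjusted mean difference between surveys will be reported with its 95% confidence interval. Histograms can stay as description. If a binary summary is wanted, for example to express relative change, keep it secondary, with a cut fixed in advance or at the baseline median.

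In section 2.4, add the detectable difference on the score scale: (1.96 + 0.84)·√(2/400) ≈ 0.20 SD at 80% power with design effect 1.5.

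The cost is wording only: no extra participants and no change to the questionnaire. It can be done before any post-intervention data exist, since that survey is planned for 2029.

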### Procedure

2.6

For each sampling route, a random point within the census section will be selected to determine the starting location for data collection. From there, a random sample of households will be chosen along the route, and finally, one individual per household will be recruited according to the quota strategy (Supplementary Table S1).

A team of four trained interviewers will conduct face-to-face the data collection in the sampled households or, when appropriate, in workplaces, as explained below. Using tablet devices, they will first provide participants a detailed explanation of the purpose of the study, the confidentiality of their responses, and their right to withdraw at any time without consequences. Written informed consent will then be obtained from all participants.

Surveys may be conducted in workplaces or other communal spaces in the community when an imbalance in the sample—particularly an under-representation of the working-age population—has been identified following household-based recruitment efforts. In this case, participation will be offered only to individuals whose residence in the study area has been previously verified.

In addition, we will have the support of the intercultural mediators, previously trained in public health by the Elche Public Health Center to address possible linguistic or cultural barriers to participation for the Arabic-speaking population. If people with communication difficulties are identified, a specific day will be organized to deal exclusively with these cases, with the assistance of one or more intercultural mediators who will assist the team of interviewers in person or by phone. These mediators will receive specific training in the administration of the questionnaire, the use of the electronic devices and compliance with the study's ethical protocol. This approach ensures the inclusion and participation of all segments of the population, including hard-to-reach persons.

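### The survey is sized with a design effect of 1.5, but the planned before–after models name no cluster or design-based variance to carry it

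*Protocol article*

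**What the plan says.** **Sample size (section 2.4).** The prevalence of interest "does not exceed 30%, with an absolute precision of ± 5% and a confidence level of 95" per cent. Then "A design effect of 1.5 has been applied", with reference to WHO STEPS guidance for complex designs, and "a rejection rate of up to 20% has been considered, implying the need to recruit at least 590 participants". For the comparison over time, "A before-and-after analysis will be conducted with 600 independent participants at each time point", said to be enough for "absolute changes of around 10%, with a confidence level of 95% and a statistical power close to 80" per cent.

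**Fieldwork (sections 2.3 and 2.6).** Census section, sex and age group define the strata and quotas. On each sampling route, "a random point within the census section will be selected to determine the starting location for data collection". Households are then drawn at random along the route, with one person taken per household. Four interviewers do the work. Workplaces or other communal spaces may be added if the household sample is unbalanced.

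**Analysis (section 2.8).** For the quality-of-life outcome, "multivariate linear regression models or Poisson regression models with robust standard errors will be used to estimate absolute and relative changes across time points". The section goes on to list the individual adjusters, province-level context variables, time interactions and the handling of missing data. It adds: "No survey weights will be used in statistical analyses". It mentions no route, venue or census-section term, no cluster-robust variance, no random effect and no survey-design estimator.

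**The concern.** A design effect in the sample size says that respondents within a sampling unit are expected to resemble one another, so that 600 interviews carry less information than 600 independent ones. An analysis that omits the same allowance reports intervals as if all 600 counted in full.

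Robust standard errors in a Poisson model for a binary outcome ordinarily correct the wrong Poisson variance. They do not correct for correlation within clusters unless a cluster variable is named. No variance correction at all is clearly attached to the linear model.

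At stake is the before–after change in the main outcome, together with the interaction models for social inequalities. Section 2.8 cautions only about type II error in small subgroups; nothing there guards against the opposite error. There is no control area, so an apparent change between waves cannot be checked against a parallel trend.

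**Working it through.** **Inputs, all from section 2.4:** prevalence 0.30, precision 0.05, z = 1.96, design effect 1.5, rejection 20%, 600 per wave, change of 10 points, power close to 80%. A two-sided test is assumed; the article does not state sidedness.

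**1. Reproducing the stated minimum of 590.**

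n = z²p(1−p)/d² = 1.96² × 0.30 × 0.70 / 0.05² = 322.7

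| Step | With design effect 1.5 | Without |
|---|---|---|
| Before rejection allowance | 484.0 | 322.7 |
| Divided by 0.8 | 605 | 403 |
| Multiplied by 1.2 | 581 | 387 |

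A finite population correction for the 36,065 residents, with division by 0.8, gives 597 to 600 with the design effect and 400 without. The stated 590 is within 3% of the results with the design effect and far from those without it. The 1.5 is therefore an active part of the plan's figure.

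**2. The power statement.** Effective n per wave = 600 / 1.5 = 400. The baseline prevalence behind the power figure is not given, so three cases are shown.

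| Change | Power, n = 400 | Power, n = 600 |
|---|---|---|
| 50% to 40% | 81.3% | 93.7% |
| 30% to 40% | 84.4% | 95.4% |
| 30% to 20% | 90.6% | 98.0% |

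Power close to 80% fits an effective 400 per wave better than 600. This supports the reading but does not prove it.

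**3. Effect of leaving the design effect (D) out of the analysis.**

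True SE / reported SE = √D

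Type I error = 2 × [1 − Φ(1.96/√D)]; coverage = 1 minus that value

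| D | SE ratio | Coverage | Type I error |
|---|---|---|---|
| 1.0 | 1.00 | 95.0% | 5.0% |
| 1.1 | 1.05 | 93.8% | 6.2% |
| 1.2 | 1.10 | 92.6% | 7.4% |
| 1.25 | 1.12 | 92.0% | 8.0% |
| 1.5 | 1.22 | 89.0% | 11.0% |
| 2.0 | 1.41 | 83.4% | 16.6% |

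**4. Does 1.5 carry over to a change between waves?** Section 2.4 applies it to one prevalence in one survey. Suppose, as an assumption, that all clustering is at census-section level, with k sections, m = 600/k interviews per section and intraclass correlation ρ = 0.5/(m − 1), which gives D = 1.5 in each wave. If section effects correlate r between waves, then:

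D(change) = 1.5 − m × ρ × r

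With k = 25 (assumed; the number of sections is not given in the text), m = 24 and ρ = 0.0217:

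| r | D(change) | Type I error |
|---|---|---|
| 0 | 1.50 | 11.0% |
| 0.5 | 1.24 | 7.8% |
| 0.9 | 1.03 | 5.4% |

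Taking k = 20 or 30 hardly alters these values. Route effects that are redrawn in each wave do not cancel in this way.

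**The case against.** The strongest reply is that silence is not a statement. The article does not say that clustering will be ignored. Robust errors can be clustered in either of the named packages. Unweighted analysis is compatible with clustered errors. The phrase about independent participants in section 2.4 means different people in each wave. A fuller analysis plan may settle the matter. A reader might therefore infer from this point that the protocol rejects cluster-adjusted errors, and the text does not support that. What remains is that section 2.8 goes as far as model family, error type, covariates, interactions, imputation and weights. Someone following it as written would run an unclustered analysis, at odds with section 2.4.

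A second reply concerns size, and much of it stands. A reader might infer that every interval and p-value will be too optimistic by exactly the factor implied by 1.5. The documents do not support this, for four reasons:

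- The 1.5 is a borrowed default, not an estimate for this district.
- Census sections are strata, which tends to lower variance. Households are a random sample along the route, so section 2.6 does not say that immediate neighbours are interviewed together.
- Route size is not given. A design effect of 1.5 needs an intra-route correlation of 0.5/(m − 1): 0.125 with 5 interviews per route, 0.056 with 10, 0.026 with 20.
- Covariates that vary within routes, such as sex and age, usually have smaller design effects than means. Adjustment for income, education and migration may also absorb part of the between-area variance.

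The article does treat p < 0.05 only as a reference and asks for caution in reading before–after results. Neither remark deals with clustering.

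**Conclusion.** The mismatch between sections 2.4 and 2.8 is real and should be corrected: the planned models do not carry the variance assumed when the survey was sized. Its consequence is conditional. If 1.5 held for the before–after contrast, type I error would be about 11% and interval coverage about 89%. With a design effect of 1.1 to 1.25 for the change, type I error would be about 6% to 8%, and with a value near 1 the loss would be negligible. These figures rest on a normal approximation, a two-sided test and no clustering adjustment in the analysis. The documents do not show which design effect will apply, so 11% is one scenario and not a forecast.

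**What to change.** State in section 2.8 that standard errors for the before–after and social-gradient models are cluster-robust on sampling route within wave. Treat each workplace or communal venue as its own cluster, since those interviews have no route. Use census section as the cluster where the baseline route identifier cannot be recovered. Apply a small-sample correction if clusters are few. Report the realised design effect for the main outcome.

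A full survey specification, with section as stratum and route as primary sampling unit, should be used only if there are at least two routes per section in each wave. With one route per section it yields no variance estimate without a workaround.

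**Cost.** Intervals may be somewhat wider. If the quoted power already rests on an effective 400 per wave, as step 2 of the working suggests, a realised design effect of up to 1.5 takes nothing from it. Baseline recruitment began on 22 October 2025, so route or venue identifiers may have to be recovered from field records; for the 2029 survey they need only be stored.
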